| Ospedale Policlinico S. Martino IRCCS                                 | Department of Surgical Sciences and Integrated Diagnostics (DISC) | Genova            | Italy       | 14-May-18       |
| Hospital General Universitario de Elche, Universidad Miguel Hernández | Colorectal & Gastrointestinal Department                          | Alicante          | Spain       | 21-May-18       |
| Manchester Royal Infirmary, University of Manchester                  | HPB Unit                                                          | Manchester        | UK          | 16-July-18      |
| Cleveland Clinic Foundation                                           | Department of Colorectal Surgery                                  | Weston (FL)       | USA         | 11-Jan-19       |

Supplementary Table 2. Functional assessment indicators

| Test                                                    | Acronym        | Range of possible scores                       | Frailty indicator threshold     | Purpose                                                                                                                |
|---------------------------------------------------------|----------------|------------------------------------------------|---------------------------------|------------------------------------------------------------------------------------------------------------------------|
| EQ 5D-3L                                                | EQ 5D-3L Index | 0-1                                            | Not applicable                  | Evaluation of QoL assessing patient's mobility, self-care, usual activities, pain and anxiety, includes a visual scale |
| EQ 5D-3L                                                | EQ 5D-3L VAS   | 0-100                                          | Not applicable                  |                                                                                                                        |
| Eastern Collaborative Oncology Group Performance Status | ECOG PS        | 0-4                                            | $\geq 1$                        | Evaluation of cancer burden on functional status                                                                       |
| Katz Activities of Daily Living                         | ADL            | 0-6                                            | $< 5$                           | Evaluation of functional independence                                                                                  |
| Mini-Cog                                                | Mini-Cog       | 0-5                                            | $\leq 2$                        | Detection of cognitive impairment in older adults therefore suitable for a more thorough evaluation.                   |
| Flemish version of the Triage Risk Screening Test       | fTRST          | 0-6                                            | $\geq 2$                        | Detection of hospitalized geriatric patients at risk for frailty                                                       |
| Timed Up & Go Test                                      | TUG            | Not applicable                                 | $\geq 20$ sec                   | Three-meters walking test to evaluate functional status                                                                |
| Geriatric 8                                             | G8             | 0-17                                           | $\leq 14$                       | Detection of onco-geriatric patients who may benefit from comprehensive geriatric assessment                           |
| Nutritional Risk Screening                              | NRS            | Normal to severely impaired nutritional status | Moderately to severely impaired | Evaluation of nutritional status taking into account BMI, weight loss and food intake                                  |
| American Society of Anesthesiology score                | ASA            | 1-5                                            | Not applicable                  | Evaluation of preoperative general clinical condition and estimation of anesthesiologic risk                           |
| Charlson Age Comorbidity Index                          | CACI           | 0-42                                           | $\geq 6$                        | Evaluation of cumulative burden of patient's comorbidities                                                             |

Supplementary Table 3. Type of surgical procedures performed

| Procedure                            | Frequency |
|--------------------------------------|-----------|
| Colectomy (left-right-subtotal)      | 434       |
| Low anterior resection of the rectum | 144       |
| Abdominoperineal resection           | 44        |
| Small bowel resection                | 5         |
|                                      |           |
| Adrenalectomy                        | 4         |
| Nephrectomy                          | 5         |
| Cystectomy                           | 3         |
| Ureter resection                     | 1         |
| Prostatectomy                        | 4         |
|                                      |           |
| Hepatectomy (segmental-lobectomy)    | 48        |
| Hepatectomy (wedge)                  | 11        |
| Common bile duct resection           | 3         |
|                                      |           |
| Lung lobectomy                       | 29        |
| Lung wedge resection                 | 3         |
| Chest wall resection                 | 2         |
|                                      |           |
| Gastrectomy total                    | 25        |
| Gastrectomy subtotal                 | 67        |
| Esophagectomy                        | 12        |
|                                      |           |
| Whipple                              | 35        |
| Pancreatectomy distal                | 4         |
| Splenectomy                          | 2         |
|                                      |           |
| Sarcoma excision                     | 5         |
|                                      |           |
| Other                                | 52        |
|                                      |           |
| Total                                | 942       |

**Supplementary Table 4. Postoperative complications**

| Complications                                       | ≤30 days           |                     | 31-90 days        |                     | 91-180 days       |                     | 0-180 days        |                     |
|-----------------------------------------------------|--------------------|---------------------|-------------------|---------------------|-------------------|---------------------|-------------------|---------------------|
|                                                     | CD*I-CDII
n (%) | CDIII-CDIV
n (%) | CDI-CDII
n (%) | CDIII-CDIV
n (%) | CDI-CDII
n (%) | CDIII-CDIV
n (%) | CDI-CDII
n (%) | CDIII-CDIV
n (%) |
| Patients with at least one complication (CD III-IV) | /                  | 128 (13.5)          | /                 | 65 (6.9)            | /                 | 52 (5.5)            | /                 | 176 (18.7)          |
| Patients with at least one complication (CD I-IV)   | 370 (39.2)         |                     | 212 (22.5)        |                     | 210 (22.2)        |                     | 494 (52.4)        |                     |
| Respiratory                                         | 53 (5.6)           | 34 (3.6)            | 24 (2.6)          | 13 (1.4)            | 26 (2.9)          | 15 (1.7)            | 69 (7.7)          | 45 (5.0)            |
| Cardiac                                             | 35 (3.7)           | 20 (2.1)            | 14 (1.5)          | 13 (1.4)            | 16 (1.8)          | 8 (0.9)             | 44 (4.9)          | 37 (4.1)            |
| Renal                                               | 54 (5.7)           | 7 (2.1)             | 15 (1.5)          | 3 (1.4)             | 10 (1.8)          | 2 (0.9)             | 66 (4.9)          | 12 (4.1)            |
| Neurological                                        | 25 (2.7)           | 1 (0.1)             | 8 (0.9)           | 6 (0.7)             | 9 (1.0)           | 2 (0.2)             | 38 (4.2)          | 8 (0.9)             |
| Nutritional                                         | 24 (2.5)           | 4 (0.4)             | 11 (1.2)          | 1 (0.1)             | 10 (1.1)          | 3 (0.3)             | 36 (4.0)          | 7 (0.8)             |
| Pressure sores                                      | 2 (0.2)            | 2 (0.2)             | 1 (1.0)           | 0 (0.0)             | 0 (0.0)           | 1 (0.1)             | 2 (0.2)           | 3 (0.3)             |
| Pain                                                | 6 (0.6)            | 2 (0.2)             | 1 (0.1)           | 2 (0.2)             | 4 (0.4)           | 2 (0.2)             | 10 (1.1)          | 3 (0.3)             |
| Delirium                                            | 11 (1.2)           | 0 (0.0)             | 3 (0.3)           | 0 (0.0)             | 0 (0.0)           | 0 (0.0)             | 13 (1.5)          | 0 (0.0)             |
| Wound                                               | 44 (4.7)           | 14 (1.5)            | 29 (3.2)          | 6 (0.7)             | 32 (3.6)          | 1 (0.1)             | 82 (9.2)          | 16 (1.8)            |
| Gastrointestinal                                    | 65 (6.9)           | 52 (5.5)            | 46 (5.0)          | 19 (2.1)            | 38 (4.2)          | 17 (1.9)            | 110 (12.3)        | 73 (8.1)            |
| Other complication                                  | 73 (7.7)           | 31 (3.3)            | 41 (4.5)          | 15 (1.6)            | 39 (4.4)          | 11 (1.2)            | 153 (17.1)        | 57 (6.4)            |

\*CD: Clavien-Dindo classification complication grade

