### **3.2 Secondary Objectives**

- To evaluate FR in terms of nutritional status, restoration of daily activities (ADL) and cognitive status (Mini-Cog)
- To evaluate 3 and 6 months postoperative morbidity and mortality
- To obtain prognostic factors for postoperative functional recovery which will assist in the treatment planning /intervention of future elderly patients who are offered surgery for cancer
- To identify variables affecting postoperative quality of life

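### Supplementary Table 4: the 0-180 day CD I-II count for Other complication (153, 17.1%) is the plain sum of its three windows and very probably counts entries, not patients

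*Protocol*

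**What the plan says.** Supplementary Table 4 gives n (%) by Clavien-Dindo (CD) grade group for three windows (up to 30 days, 31-90 days, 91-180 days) and for the whole period of 0-180 days. The residual category reads "Other complication | 73 (7.7) | 31 (3.3) | 41 (4.5) | 15 (1.6) | 39 (4.4) | 11 (1.2) | 153 (17.1) | 57 (6.4"). The gastrointestinal row, the nearest in size, reads "Gastrointestinal | 65 (6.9) | 52 (5.5) | 46 (5.0) | 19 (2.1) | 38 (4.2) | 17 (1.9) | 110 (12.3) | 73 (8.1").

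Two summary rows head the table, and their labels name patients as the unit, for example "Patients with at least one complication (CD I-IV"). The category rows carry no counting rule. The table's only footnote expands the abbreviation CD.

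Section 3.2 of the protocol lists among the secondary objectives: "To evaluate 3 and 6 months postoperative morbidity and mortality".

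**The concern.** Over a six-month period, a patient with a complication in two windows should count once in the 0-180 day column. The total for the period should then usually be smaller than the three windows added together. The summary rows and nearly all category cells behave that way. The Other complication row does not: in both grade groups its 0-180 day figure is exactly the sum of the windows, although its CD I-II windows hold more entries than those of any other category.

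The percentages beside these counts use the same denominator as the neighbouring rows. A reader will therefore take 17.1% as the share of patients affected and set it against 12.3% for gastrointestinal complications. If one figure counts entries and the other counts patients, the comparison is not like for like, and a reported component of six-month morbidity is too high.

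**Working it through.** **Inputs.** All counts come from Supplementary Table 4. A window entry here means one patient counted in one window.

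**1. Reproduce the printed cells.**
- CD I-II: 73 + 41 + 39 = 153; printed 153.
- CD III-IV: 31 + 15 + 11 = 57; printed 57.

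**2. Make the same comparison in every other row** (0-180 day count / sum of the three windows).

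| Row | CD I-II | CD III-IV |
|---|---|---|
| Respiratory | 69/103 | 45/62 |
| Cardiac | 44/65 | 37/41 |
| Renal | 66/79 | 12/12 |
| Neurological | 38/42 | 8/9 |
| Nutritional | 36/45 | 7/8 |
| Pressure sores | 2/3 | 3/3 |
| Pain | 10/11 | 3/6 |
| Delirium | 13/14 | 0/0 |
| Wound | 82/105 | 16/21 |
| Gastrointestinal | 110/149 | 73/88 |
| Ten rows pooled | 470/616 = 0.763 | 204/250 = 0.816 |
| **Other** | **153/153** | **57/57** |

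All ten CD I-II ratios are below 1, from 2/3 = 0.67 to 13/14 = 0.93. In CD III-IV, three small cells also equal their sums (renal 12, pressure sores 3, delirium 0). No row except Other equals its sum in both columns. The summary rows are well below theirs: 494 against 370 + 212 + 210 = 792, and 176 against 128 + 65 + 52 = 245.

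**3. Check the denominator.** 153/0.171 = 895 and 110/0.123 = 894. The Other percentage is on the same patient base as gastrointestinal.

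**4. Could there simply be no overlap?** Suppose the windows are independent draws from N patients, with sizes a, b and c. The probability that nobody appears twice is

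P = [C(N−a, b)/C(N, b)] × [C(N−a−b, c)/C(N, c)].

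At N = 895:
- CD I-II (73, 41, 39): P = 0.00012. It is 0.00007 at N = 850 and 0.0002 at N = 942.
- CD III-IV (31, 15, 11): P = 0.33. It is 0.31 at N = 850 and 0.35 at N = 942.

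**5. How many distinct patients might the CD I-II cell hold?**
- Hard bounds: at least the largest window, 73 (73/895 = 8.2%), and at most the sum, 153 (17.1%).
- Independent windows: N × [1 − (1 − a/N)(1 − b/N)(1 − c/N)] = 895 × [1 − (822/895)(854/895)(856/895)] = about 145 (16.2%). Overstatement 153/145 = 1.06, about 6%.
- Overlap as in the other rows (assumption): 153 × 0.67 = 103 (11.5%) to 153 × 0.93 = 142 (15.9%). Overstatement 153/142 = 1.08 to 1/(2/3) = 1.50, so about 8% to 50%. The pooled ratio gives 153 × 0.763 = 117 (13.1%).

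**6. Does the order of categories change?** Other would fall below gastrointestinal in CD I-II only if its ratio were under 110/153 = 0.72. The pooled estimate (117) and the independence estimate (145) both stay above 110.

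**The case against.** The strongest reply is that no stated rule is broken. Only the summary rows are labelled as patients. That the category rows count each patient once is inferred from totals that fall short of their sums. The value 153 is also possible in itself: it is well below the 494 patients with any complication, and a mixed residual category need not recur within patients as a single organ system does. This stands as a limit on proof. The cell is a strong anomaly, and only patient-level data can show that it is an error. It does not explain the cell away: two different events of this kind in one patient still make one patient, and even independent windows would almost never give zero overlap among 153 entries.

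The second reply concerns the CD III-IV cell, and it stands. Zero overlap among 57 entries has a probability of about one in three, and three small cells in that column also equal their sums. A reader might infer that both cells are shown to be wrong. The numbers support that for CD I-II only. For CD III-IV the one added reason for doubt is that the same row shows the same pattern twice.

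A reader might also infer that Other leads the table only because of the counting. The figures do not support this. In CD I-II it probably stays at or near the top after a recount, and in CD III-IV gastrointestinal already leads as printed, "110 (12.3) | 73 (8.1") against "153 (17.1) | 57 (6.4") for Other.

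**Conclusion.** The concern holds for one cell. The 0-180 day CD I-II count for Other complication very probably adds window entries and shows them as a percentage of patients. The relative overstatement is roughly 6% to 50%. The low end assumes independent windows, and the high end assumes the strongest overlap seen in another row, which rests on only three entries (pressure sores). The pooled ratio would give about 31%, but that is one point in a wide range and should not be quoted as the size of the error. The certain statement is that the count lies between 73 and 153.

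The CD III-IV cell deserves a check and no more. It would also go too far to conclude that six-month morbidity as a whole is misreported. The summary rows, 494 (52.4%) and 176 (18.7%), are clearly not sums of windows, and nothing here puts them in doubt. The EQ VAS primary endpoint (section 6.1) and the sample size (section 6.2) are not touched. Severity is minor: one row of a results table that bears on a secondary objective.

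**What to change.** Recount the 0-180 day CD I-II cell of the Other complication row from patient-level data, counting each patient once per grade group. Check the CD III-IV cell in the same run. Correct n and % where they change. If the recount confirms that no patient had an event of this kind in more than one window, keep the figures and say so in a footnote. In either case, state in the table that category rows count patients with at least one event in the period.

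The cost is one rerun of the table and a corrected page, with no new data. The Other CD I-II percentage will probably fall.

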**Health Questionnaire**  
**English version for the UK**  
**(Validated for Ireland)**

Under each heading, please tick the ONE box that best describes your health TODAY.

**MOBILITY**

- I have no problems in walking about ☐
- I have some problems in walking about ☐
- I am confined to bed ☐

**SELF-CARE**

- I have no problems with self-care ☐
- I have some problems washing or dressing myself ☐
- I am unable to wash or dress myself ☐

**USUAL ACTIVITIES (e.g. work, study, housework, family or leisure activities)**

- I have no problems with performing my usual activities ☐
- I have some problems with performing my usual activities ☐
- I am unable to perform my usual activities ☐

**PAIN / DISCOMFORT**

- I have no pain or discomfort ☐
- I have moderate pain or discomfort ☐
- I have extreme pain or discomfort ☐

**ANXIETY / DEPRESSION**

- I am not anxious or depressed ☐
- I am moderately anxious or depressed ☐
- I am extremely anxious or depressed ☐

We would like to know how good or bad your health is TODAY.

This scale is numbered from 0 to 100.

100 means the best health you can imagine.  
0 means the worst health you can imagine.

Please mark an X on the scale to indicate how your health is TODAY.

Now, write the number you marked on the scale in the box below.

YOUR HEALTH TODAY =

[figure not shown]

Supplementary Figure 1. The EQ-5D-3L.

[figure not shown][figure not shown][figure not shown]

## ABBREVIATIONS

|        |                                                                     |
|--------|---------------------------------------------------------------------|
| AE     | Adverse event                                                       |
| AR     | Adverse reaction                                                    |
| CC     | Coordinating Center                                                 |
| CI     | Chief Investigator                                                  |
| CRA    | Clinical Research Associate (Monitor)                               |
| CRF    | Case Report Form                                                    |
| CRO    | Contract Research Organisation                                      |
| CT     | Clinical Trials                                                     |
| CTC    | Common toxicity criteria                                            |
| ECOG   | Performance status (Eastern Cooperative Oncology Group, ECOG Scale) |
| FR     | Functional recovery                                                 |
| GCP    | Good Clinical Practice                                              |
| IB     | Investigators Brochure                                              |
| ICF    | Informed Consent Form                                               |
| ICH    | International Conference of Harmonisation                           |
| IDMC   | Indipendent Data Monitoring Committee                               |
| IEC    | Independent Ethics Committee                                        |
| IMP    | Investigational Medicinal Products                                  |
| IRB    | Independent Review Board                                            |
| PI     | Principal Investigator                                              |
| QoL    | Quality of Life                                                     |
| RECIST | Response Evaluation Criteria In Solid Tumors                        |
| SAE    | Serious Adverse Event                                               |
| SAR    | Serious Adverse Reaction                                            |
| SOP    | Standard Operating Procedure                                        |
| SUSAR  | Suspected Unexpected Serious Adverse Reactions                      |
| WHO    | World Health Organization                                           |

## **1. BACKGROUND**

Progressive aging of the world population has become one of the most significant challenges for national health care systems. With aging, the incidence and prevalence of cancer increases: it has been estimated that in 2020 more than 60% of all malignancies will occur in patients aged 70-year and older. At the same time, progress in medical knowledge has determined an extremely positive impact in clinical practice. In particular, improvements in perioperative care, surgical minimally invasive techniques and the introduction of multimodal treatment have made surgery feasible for a higher number of patients. Nevertheless, several studies show that senior adults affected by cancer are often treated sub-optimally, above all in the surgical field.

It is well known that onco-geriatric patients are at higher risk of developing postoperative complications because they are often affected by multiple comorbidities. It has been reported that up to 80% of elderly patients might experience a surgical complication. Thus, after major surgery, patients may be at risk of both developing postoperative complications, and suffering major discomfort that can negatively affect postoperative quality of life.

The vast majority of research studies are focused on short-term outcomes and do not explore long- term disability or postoperative quality of life.

Onco-geriatric patients represent a challenge for surgical oncologists because, despite the evidence that comorbidities are often responsible for poor postoperative outcomes, patients' selection has not been completely standardized yet. Preoperative assessment of the functional status is fundamental to identify fit, vulnerable and frail individuals in order to avoid under- or over-treatment. Functional recovery has been shown to be of critical value in the elderly population since restoration/conservation of independence is probably the most important end-point for senior adults. Individualization of elderly cancer-patients care is closely related with the possibility of preserving their functional capacity. We could conclude that for elderly patients, perhaps more than anyone else, "quality" is more important than "quantity" of life.

